## Abstract

**Background:**

A smoking ban was implemented across all prisons in Queensland, Australia, in May 2014, with the aim of improving the health of prisoners and prison staff. However, relapse to smoking after release from prison is common. Only one previous study, conducted in the United States, has used a randomised design to evaluate an intervention to assist individuals in remaining abstinent from smoking following release from a smoke-free prison.

**Methods:**

This paper describes the rationale for and design of a randomised controlled trial of an intervention to extend smoking abstinence in men after release from smoke-free prisons in the state of Queensland, Australia. Participants in the intervention group will receive a brief intervention involving four group sessions of motivational interviewing and cognitive behavioural therapy, initiated 4 weeks prior to release from prison. The comparison group will receive a pamphlet and brief verbal intervention at the time of baseline assessment. Assessment of self-reported, post-release smoking status will be conducted by parole officers at regular parole meetings with the primary outcome measured at 1 month post release.

**Discussion:**

The prevalence of smoking and related health harms among people who experience incarceration is extremely high. Effective interventions that result in long-term smoking cessation are needed to reduce existing health disparities in this vulnerable population.

**Trial registration:**

Current Controlled Trials ACTRN12616000314426

## Background

Tobacco smoking is a global public health issue, killing approximately six million people annually (World Health Organisation, 2015). It is a major risk factor for many physical disorders such as coronary heart disease, cancer, and strokes (AIHW, 2014a). In Australia, tobacco is responsible for 7.8% of the total burden of disease and injury—making it the greatest single contributor to the burden of disease in the country (Begg et al., 2007). Fortunately, the health benefits of quitting tobacco smoking are both substantial and rapid (Zwar et al. 2014).

Despite declining levels of tobacco smoking in Australia’s general population (AIHW, 2014b), the prevalence of smoking has remained stubbornly high for Australian prisoners—74% of whom smoke (AIHW, 2015), a rate which is five times that in the general population (AIHW, 2014a). One reason for the high prevalence of smoking in prisoners is that groups with a high prevalence of smoking in the community—such as Indigenous people, people with a mental illness, people who inject drugs, and people from socio-economically disadvantaged backgrounds—are also at increased risk of incarceration (AIHW, 2013a, 2013b, 2015; Belcher et al. 2006). The high prevalence of tobacco consumption among prisoners contributes significantly to increased age-adjusted mortality rates and years of potential life lost, when compared to the general population (Binswanger et al., 2014; Kinner, Forsyth, et al. 2013; Kinner, Lennox, et al. 2013), and to some of the worst health outcomes out of any identifiable population group (Maruschak & Beck, 2001; Richmond et al., 2013a).

In an effort to improve prisoners’ health, smoking bans have been implemented in many prisons around the world. However, despite short-term benefits associated with smoking bans (Binswanger et al., 2014), the majority of prisoners return to smoking upon release (Clarke et al., 2013; Lincoln et al. 2009), suggesting that these bans result in short-term tobacco abstinence only (Donahue, 2009). Furthermore, recent studies (Cropsey & Kristeller, 2005; Kauffman et al. 2011) suggest that not all prisoners adhere to smoking bans. This suggests the need for efforts to promote smoking cessation both in and, critically, after release from prison, to reduce rates of tobacco-related morbidity and mortality among ex-prisoners (Belcher et al., 2006; Djachenko et al. 2015; Gautam et al. 2011; Kauffman et al., 2011; Mackay, 2014).

There is good evidence for the effectiveness of Cognitive Behavioural Therapy (CBT; Killen et al., 2008; Stead & Lancaster, 2005; Webb Hooper et al. 2010) and Motivational Interviewing (MI; Lindson-Hawley et al. 2015) for promoting smoking cessation, particularly when delivered in a group format (Stead & Lancaster, 2005). However, no studies have evaluated the effectiveness of a group-based combined CBT and MI intervention for promoting smoking abstinence in ex-prisoners, and only one previous study has rigorously evaluated an intervention designed to maintain smoking abstinence after release from a smoke-free prison. The Working Inside for Smoking Elimination (WISE) study (Clarke et al., 2013) used a randomised design to evaluate the effectiveness of individual intervention sessions, based on principles of both CBT and MI, for improving smoking abstinence after release from a smoke-free prison in the state of Rhode Island, USA. This study found a modest yet significant effect; 12% of the intervention group remained abstinent from tobacco at 3 months post-release, compared with only 2% of the control group.

The aim of this study is to evaluate the effectiveness of a group-based version of the WISE intervention for maintaining smoking abstinence among men in the first 3 months after release from smoke-free prisons in Queensland, Australia.

## Methods

### Study Design

The study is a randomised controlled trial comparing two groups of soon-to-be released male prisoners. Three hundred sentenced prisoners will be recruited from four correctional centres in Queensland. Intervention group participants will take part in four group sessions of CBT and MI encouraging smoking abstinence post release, in the 4 to 6 weeks prior to release from prison. The comparison group will receive usual care plus a pamphlet encouraging smoking abstinence and a brief verbal explanation of the pamphlet at baseline. After individual baseline screening interviews assessing smoking history and future smoking intentions, participants will be randomised 1:1 to the intervention or comparison group. Once participants are released from custody, parole officers will record their self-reported smoking status at every appointment, for a maximum of 3 months. The primary outcome is point-prevalence of tobacco smoking abstinence at 1 month post-release. This study has been approved by the Griffith University Human Research Ethics Committee and by the Queensland Corrective Services (QCS) Research Committee. The trial is registered with the Australian New Zealand Clinical Trials Registry (ACTRN12616000314426) (Fig. 1).

**Fig. 1 Fig1:**
[figure not shown]
Overview of study design

### Recruitment and inclusion criteria

Three hundred male prisoners will be recruited from four correctional centres in the populous south-east corner of Queensland, Australia. Queensland was the second Australian jurisdiction to implement a smoking ban across all correctional institutions, on 5 May 2014 (Mackay, 2014). Smoking cessation support was provided to staff and prisoners in the form of free nicotine replacement therapy (NRT) and access to telephone counselling.

QCS will identify all prisoners at the four selected correctional centres who fulfil the following eligibility criteria: age 18 years old or older; male; incarcerated after the smoking ban was introduced (5 May 2014); have been incarcerated continuously for at least 4 weeks (so as to have passed tobacco withdrawal); due to be released from custody within 4 to 6 weeks; and will be released to a minimum of 1 month of court-ordered parole.

Eligible prisoners will be identified by prison staff and provided with an information sheet that provides details of the study. If the eligible prisoner is interested in participating, he will be shown to a private interview room, where the researcher will obtain informed consent and undertake the baseline assessment. Randomisation will occur at conclusion of the baseline assessment.

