### Measures

The baseline assessment will be administered individually to all participants and will take 15–20 min to complete. It measures participants’ smoking history, overall health status, drug use history, nicotine dependence (using the Fagerström Test for Nicotine Dependence; Fagerstrom & Schneider, 1989), and post-release smoking intentions and desires. The assessment was designed by the authors and informed by previous research (e.g. Clarke et al., 2011, 2013; Richmond et al. 2013a, 2013b).

Once participants have been released from prison, parole officers will assess participants’ self-reported smoking status at each appointment, using four questions: 1) Have you smoked since release? 2) If yes, how many weeks ago did you first smoke? 3) Are you currently smoking? 4) If yes, how many cigarettes do you smoke on average per day? In this way, absolute smoking status, duration of smoking abstinence, and intensity of the relapse (e.g., quantity of cigarettes smoked per day) can be measured. These questions also account for situations where a participant may have had a ‘lapse rather than a relapse’ (e.g., temporarily resumed smoking, then returned to abstinence).

Most parolees meet with their parole officers weekly, but some meet fortnightly or monthly. Parole officers will assess parolees’ smoking status at every meeting, but all participants will be assessed at 1 month post-release (the primary endpoint). Parole officers will continue to ask these four questions at each meeting with the participant for up to 3 months post-release. The rationale for a 3-month end point is that the majority of smoking relapses occur within the first 3 months post-release (Ockene et al., 2000). Clarke et al. (2013) also support this relatively brief follow-up period due to the high relapse rates immediately after release. Although restricting the study to parolees may have implications for generalisability, this is offset by an expected low rate of attrition, since most parolees are expected to attend most of their parole meetings.

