### Outcomes

The primary outcome of this study is point-prevalence tobacco abstinence at 1 month post-release, measured by self-report. Secondary outcomes include number of weeks to first cigarette after release, amount of tobacco consumed in the event of relapse, and point-prevalence of tobacco abstinence at 3 months post-release. Participants lost to follow-up will be considered non-abstinent—the most conservative assumption.

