Although this will be, to the best of our knowledge, the second ever randomised trial of an intervention to promote smoking cessation after release from prison, the protocol has some limitations. First, the trial is unblinded, but given the nature of the intervention and the follow-up, blinding is not feasible in this setting. Second, we note that some degree of contamination between the intervention and comparison groups in the prison setting is likely, but is unfortunately unavoidable in this situation. The consequence of any contamination would be to attenuate the intervention effect, such that the trial would be a conservative test of the intervention. Third, given high rates of reincarceration among ex-prisoners in Australia (Steering Committee for the Review of Government Service Provision, 2016), some proportion of participants may return to prison during follow-up. By making our primary endpoint only 1 month post-release we aim to minimise this form of potentially biased attrition. Fourth, the results may not be generalisable to all ex-prisoners, including to important subgroups such as women, people with an intellectual disability, ex-prisoners not on parole, and remandees (pre-trial detainees). Fifth, we rely on parole officers to collect follow-up data, which is likely to substantially reduce loss to follow-up but, despite the fact that tobacco smoking is not a prohibited behaviour for parolees, may impact on the data quality where good rapport cannot be established between parole officers and parolee participants. Sixth, our outcome will be measured by self-report, without biological verification. Although there is a possibility of self-report bias, tobacco smoking is not prohibited for parolees, and studies using both self-report and tobacco abstinence validation tests (e.g. presence of cotinine in urine) show that self-report can be a reliable measure of smoking abstinence (Clarke et al., 2013; Richmond et al., 2013b; Short et al., 2009).

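### Entry needs only 1 month of parole, but the 3-month secondary outcome is observed only at parole meetings, so on the plain reading men whose parole ends sooner are scored as smokers

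*Protocol article*

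**What the plan says.** Four parts of the Protocol article bear on this.

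- **Eligibility** (Recruitment and inclusion criteria): the man "will be released to a minimum of 1 month of court-ordered parole". No 3-month minimum is set.
- **Data source** (Study Design; Measures; Discussion): "parole officers will record their self-reported smoking status at every appointment, for a maximum of 3 months", and "Parole officers will continue to ask these four questions at each meeting with the participant for up to 3 months post-release". Among its limitations the article says "we rely on parole officers to collect follow-up data". It describes no other contact route after release.
- **Outcome and time horizon** (Outcomes; Background): the secondary outcomes include "point-prevalence of tobacco abstinence at 3 months post-release", and the aim is framed as "maintaining smoking abstinence among men in the first 3 months after release from smoke-free prisons".
- **Missing data** (Outcomes): "Participants lost to follow-up will be considered non-abstinent". The term is not defined, and no exception is made for parole that has run its course.

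The primary outcome is abstinence at 1 month, which falls within the minimum parole period.

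**The concern.** A man with at least 1 but less than 3 months of parole has no parole meeting at 3 months. His value is missing because of the length of a court order that was settled before he was randomised, not because of anything he did afterwards. Scoring a missing man as a smoker is a defensible convention when non-attendance may itself signal relapse. An expired court order carries no such signal.

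At stake is the meaning of the 3-month result. Under the rule, the reported rates would depend partly on how the courts set parole length. Both arms' abstinence and the absolute benefit would be understated at the horizon named in the trial's aim.

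**Working it through.** **The plan's own figure.** There is none to reproduce. The article gives no distribution of parole length and no 3-month power. The check therefore shows how the rule acts over an assumed range.

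**Inputs**
- 3-month abstinence of 12% vs 2%: the earlier trial's result in the Background, used as illustration.
- 23% vs 14%: the design rates in Sample size calculation, used as a second illustration.
- 300 men randomised 1:1, so 150 per arm (Study Design); one-sided 5% test (Planned Analyses).
- f, the share of men with parole under 3 months: not in the document. Assumed 10% to 50%, equal in both arms, and unrelated to abstinence and to the intervention effect.

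**Step 1: the rates.** Men with short parole contribute no abstainers, so

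scored rate = (1 − f) × true rate, and scored difference = (1 − f) × true difference.

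| f | 12% becomes | 2% becomes | Difference (points) | Ratio |
|---|---|---|---|---|
| 0 | 12.0% | 2.0% | 10.0 | 6.0 |
| 10% | 10.8% | 1.8% | 9.0 | 6.0 |
| 25% | 9.0% | 1.5% | 7.5 | 6.0 |
| 40% | 7.2% | 1.2% | 6.0 | 6.0 |
| 50% | 6.0% | 1.0% | 5.0 | 6.0 |

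The factor (1 − f) cancels in the ratio. If the true rates are equal, the scored rates are equal too, so the test remains valid under the null.

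**Step 2: does restriction cost power?** Compare (a) scoring short-parole men as smokers, with 150 per arm and the shrunken rates, and (b) restricting to longer parole, with about 150 × (1 − f) per arm and the true rates. The normal approximation is

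power = Φ{ [Δ − 1.645 √(2p̄(1 − p̄)/n)] / √([p₁(1 − p₁) + p₂(1 − p₂)]/n) }, where Δ = p₁ − p₂ and p̄ is the mean of the two rates.

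Example at f = 50%, 12% vs 2%:
- (a) n = 150, 6% vs 1%, p̄ = 0.035: (0.05 − 1.645 × 0.02122)/0.02102 = 0.718, so power is 76%.
- (b) n = 75, 12% vs 2%, p̄ = 0.07: (0.10 − 1.645 × 0.04167)/0.04086 = 0.770, so power is 78%.

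| Rates | f | (a) Scored as smokers | (b) Restricted |
|---|---|---|---|
| 12% vs 2% | 25% | 90% | 91% |
| 12% vs 2% | 40% | 83% | 84% |
| 12% vs 2% | 50% | 76% | 78% |
| 23% vs 14% | 50% | 38% | 41% |

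Exact enumeration of the same one-sided test gives a different level for 12% vs 2% but the same comparison: 93% vs 94% at f = 25% and 83% vs 84% at f = 50%. For 23% vs 14% at f = 50% it gives 38% vs 42%. Restriction corrects the estimate and costs essentially no power. It also gains little.

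**The case against.** The strongest reply is that the plan already allows for variable follow-up. It speaks of up to, or a maximum of, 3 months and guarantees an assessment only at 1 month. A man who completes a shorter planned window need not be lost to follow-up, and the definition could sit in a full protocol or SAP that is not shown. This stands in part: counting parole expiry as loss is the plain reading of the rule, not an explicit statement. But the article itself fixes the entry criterion, the data source, a 3-month outcome and an imputation rule without exceptions, and it leaves these men with no other treatment. The expectation of low attrition in Measures rests on attendance at meetings and cannot cover men who have none left.

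A reader might infer more than the document supports:

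- **That the primary result is compromised.** It is not; the 1-month endpoint lies inside the minimum parole period.
- **That the rule favours one arm.** Parole length is fixed before randomisation, so f is equal in expectation. A chance imbalance is random error, which the test's alpha already covers, and not bias.
- **That the survival analysis counts parole expiry as relapse.** Planned Analyses does not say so. It names discrete-time survival analysis and gives no event or censoring rule for this case.
- **That a planned comparison with the earlier trial is distorted.** The 12% vs 2% is background, and no formal comparison is planned.

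It is also fair that restriction changes whom the 3-month result describes and hardly changes the inference.

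**Conclusion.** The concern holds for the 3-month secondary outcome. On the plain reading of the loss-to-follow-up rule, men whose parole ends before 3 months are scored as smokers whatever they reported, and both rates and the absolute difference shrink by the factor (1 − f). With 12% vs 2%, the 10-point difference becomes 7.5 points at f = 25% and 5 points at f = 50%.

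The size rests on assumptions. The value of f is not given and could be near zero. It is taken as equal in both arms, and parole length as unrelated to abstinence and to the intervention effect. If it is related, (1 − f) still multiplies the rates among men with longer parole, but those need not equal the rates for all men.

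Severity is moderate: a secondary outcome is misestimated, while the primary outcome and the validity of the 3-month test under the null are sound.

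**What to change.** 1. Record the court-ordered parole end date at baseline, before randomisation.
2. For 3-month abstinence, analyse men whose court-ordered parole, as fixed before randomisation, is at least 3 months. Selecting on a pre-randomisation variable keeps the comparison randomised. Within that set, keep scoring men who miss the assessment as non-abstinent.
3. State that parole expiry is not loss to follow-up.
4. In the discrete-time survival analysis, state that men without relapse are censored at their last parole meeting when parole ends.

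The cost is wording and one extra baseline item. The 3-month denominator becomes smaller (about 112 per arm at f = 25%, 75 at f = 50%), and the 3-month result then applies to men with longer parole, which the report should say. The date is best captured prospectively, so this should be settled before recruitment or early in it.

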### Groups and intervention

Intervention group participants will receive four weekly group sessions of the intervention in the 4 weeks prior to their release. They will be assigned to a group depending on their release date, ensuring that all members of each group are due for release at a similar time. Each group will consist of between four and six participants. Each intervention session will be approximately 40–60 min in duration, and will be arranged at dates and times that are convenient to the prisoners and prison staff.

Consistent with the WISE study (Clarke et al., 2013), sessions one and four will be based on principles of MI, and sessions two and three on CBT. MI sessions will focus on aiding the development of self-efficacy and personal choice, and on addressing group members’ ambivalence towards remaining abstinent from smoking post-release. The CBT sessions will teach participants to recognise specific environmental and event triggers to smoking and identify behavioural and coping strategies in response to these triggers. The intervention session plan is based on the successful WISE intervention delivered by Clarke et al. (2013) and has been adapted based on recommendations by a clinical psychologist with extensive experience in Australian correctional settings. Sessions will be delivered by the primary researcher, who has a background in psychology and counselling and has received further training in CBT and MI techniques.

Prisoners in the comparison group will receive a pamphlet at the end of the baseline assessment, as well as a brief (1 to 2 min) verbal explanation of the pamphlet. The pamphlet highlights the advantages of staying abstinent from smoking post-release, and provides tips for doing so.

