### Sample size calculation

Sample size calculations were informed by the work of Clarke et al. (2013) who, based on a comprehensive review of the literature, conservatively estimated abstinence rates of 23% for the intervention group and 14% for the control group. With alpha of .05 one-tailed and a power level of at least .80, these estimates result in a desired sample size of 292, which we have rounded up to 300 participants. These estimates are considered conservative for two reasons. First, whereas participants in the study by Clarke et al. (2013) did not receive any cessation support from prison authorities, prisoners in Queensland receive a week’s supply of free nicotine patches upon incarceration, associated with long-term smoking abstinence (Stead et al., 2012; Wu et al. 2006). Second, the observed intervention effect in the study by Clarke et al. (2013) was larger than expected (25% vs. 7% at 3 weeks), and the intervention in this trial is an enhanced version of the WISE intervention.

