### Randomisation

After baseline assessment, each participant will be randomised 1:1 to the intervention or comparison group. Randomisation will be stratified by prison. The number of participants in each group per prison will reflect the sample distribution across the four prisons. Randomisation will also be stratified by intention to quit, given evidence (Thibodeau et al. 2010) that prisoners who have an intention to quit are more likely to remain abstinent post-release. The randomisation list will be divided into randomly permuted blocks of size 4, 6, or 8. Within each block, an equal number of intervention and comparison conditions will be assigned. Use of random permuted blocks ensures balance during assignment and helps to prevent participants from guessing which condition they have been assigned to (Beller et al. 2002). At this stage, the number of prisoners who intend to remain abstinent from smoking after release is unknown.

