### Planned Analyses

For the primary outcome, the primary analysis will be an intention to treat analysis, with a *p*-value of <0.05 from a one-tailed chi square test of proportions considered statistically significant. The secondary analysis will be a per protocol analysis, excluding intervention group participants who did not attend at least three of the four intervention sessions. Secondary outcomes will be examined using chi square tests (for categorical variables), independent samples t-tests (for continuous variables) and discrete time survival analysis (for time to relapse).

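### The intervention is delivered in therapy groups but the comparison is not, and the fixed primary chi-square test makes no allowance for correlation that the sessions may create

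*Protocol article*

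**What the plan says.** All references are to the protocol article.

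- **Randomisation:** allocation is by individual; "each participant will be randomised 1:1 to the intervention or comparison group".
- **Groups and intervention, active arm:** "Intervention group participants will receive four weekly group sessions of the intervention in the 4 weeks prior to their release". Men are put into a group by release date, after allocation. On size: "Each group will consist of between four and six participants". On delivery: "Sessions will be delivered by the primary researcher".
- **Groups and intervention, other arm:** "Prisoners in the comparison group will receive a pamphlet at the end of the baseline assessment", with a verbal explanation of 1 to 2 minutes. The baseline assessment is individual, so this arm has no therapy groups.
- **Planned Analyses:** the primary intention-to-treat analysis requires p < 0.05 from a "one-tailed chi square test of proportions considered statistically significant". Secondary outcomes use chi-square tests, independent-samples t-tests and discrete-time survival analysis.
- **Sample size calculation:** the inputs are two rates, alpha and power only.

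The article mentions no within-group correlation, ICC or design effect. The limitations in the Discussion cover contamination between arms but not clustering within therapy groups.

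**The concern.** This is a partially nested design: individual randomisation, with group treatment in one arm only. Men who attend the same four sessions can influence one another, and sessions can go better in one group than in another. The Discussion itself presents the group format as an enhancement over individual delivery, so the group is meant to matter. If these influences make outcomes within a group more alike, the variance of the intervention-arm proportion exceeds the binomial variance that the chi-square test uses. The comparison arm is unaffected.

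The consequence would be a p-value that is somewhat too small for the primary result, against a threshold that is already one-tailed 0.05. The t-tests and the survival analysis make the same assumption. The article names the primary test, its sidedness and its threshold, so this is a stated choice and not a detail left to a later document.

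**Working it through.** **Inputs from the article.** 300 men randomised 1:1, so 150 per arm. Group size m = 4 to 6, so 150/6 = 25 to 150/4 ≈ 38 groups; m = 5 gives 30. The planning rates are "conservatively estimated abstinence rates of 23% for the intervention group and 14% for the control group". Alpha is 0.05 one-tailed (z = 1.645).

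**Assumed.** The ICC is the correlation created by the sessions in the intervention arm. The article gives none; 0.02, 0.05 and 0.10 are shown.

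**1. The plan's own figure, without clustering.** Per-arm n = [z_α√(2p̄q̄) + z_β√(p₁q₁ + p₂q₂)]² / d², with p̄ = 0.185, d = 0.09 and z_β = 0.842.
- One-tailed: (1.645 × 0.5491 + 0.842 × 0.5454)² / 0.0081 gives 230 per arm, 460 in total.
- The stated total of 292 is not reproduced. It equals the two-sided per-arm number (292 per arm, 584 in total).
- With 150 per arm, one-tailed power is about 64% (pooled formula) or 64.7% (unpooled, used below). This shortfall is there at ICC = 0 and is a separate matter.

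**2. Design effect, intervention arm only.** DEFF = 1 + (m − 1) × ICC. For m = 5 this is 1.08, 1.20 and 1.40.

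**3. Type I error of the plain test, equal rates.** The ratio of true to naive SE is √((1 + DEFF)/2), and true alpha = 1 − Φ(1.645 / ratio).
- ICC 0.02: ratio √1.04 = 1.020, alpha 5.3%
- ICC 0.05: ratio √1.10 = 1.049, alpha 5.8%
- ICC 0.10: ratio √1.20 = 1.095, alpha 6.7%

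A beta-binomial simulation (30 groups of 5 against 150 independent men, rate 14%, 200,000 trials) gave 5.4%, 5.8% and 6.6%. By formula, groups of 4 give 5.3%, 5.6% and 6.3%, and groups of 6 give 5.4%, 6.1% and 7.1%.

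**4. Standard error and power at 23% versus 14%.** True variance = (0.1771 × DEFF + 0.1204)/150; naive variance = 0.2975/150. Power of a test using the true SE = Φ(0.09/SE − 1.645).

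| ICC | True SE | True/naive SE | Power | Loss from 64.7% |
|---|---|---|---|---|
| 0 | 0.0445 | 1.00 | 64.7% | – |
| 0.02 | 0.0456 | 1.02 | 62.9% | 1.8 points |
| 0.05 | 0.0471 | 1.06 | 60.5% | 4.2 points |
| 0.10 | 0.0496 | 1.11 | 56.8% | 7.9 points |

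**5. Shared prison and release period.** Both arms have these. If a common effect is balanced across arms within release cohorts (an assumption), the variance of the difference is multiplied by (1 − ICC), and alpha = 1 − Φ(1.645/√(1 − ICC)). That gives 4.8%, 4.6% and 4.1% at ICC 0.02, 0.05 and 0.10. This source makes the plain test slightly conservative.

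**The case against.** The strongest reply is that the usual reasons for clustering are largely absent.

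- **Prison and release period.** Both are common to the two arms, and randomisation is stratified by prison. Step 5 shows that correlation of this kind does not inflate the error. This stands. Only effects that arise after randomisation, from being in a particular group, count.
- **Therapist.** One researcher delivers every session, so variation between therapists adds nothing. This stands. Group interaction and session-to-session variation remain as sources.
- **No effect on anyone.** If the sessions change nobody's outcome, individual randomisation keeps the chi-square test valid. This also stands. Inflation needs groups to differ while the average effect is nil.
- **Strata.** The plain test ignores the stratification factors (prison and intention to quit), which pushes mildly towards conservatism.
- **An analysis plan may exist.** This carries less weight, because the article already fixes the primary test.

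A reader might infer more than the documents support. One such reading is that the trial's error rate is certainly wrong. The article gives no ICC, and type I error as high as 8.2% (groups of 5) needs an ICC of 0.20, for which nothing in the article argues. A second is that clustering explains why power is near 65% when at least 80% is claimed; step 1 shows that this gap is there before any clustering. A third is that the groups are closed. Fixed membership is a reasonable inference from grouping by release date and a four-session course, but the article does not state it. Finally, the article specifies a p-value and no confidence interval, so the point about precision applies to any interval reported later, not to a planned one.

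**Conclusion.** The point holds in a conditional and modest form. The design is partially nested, and the stated primary test has no term for it. Whenever the sessions induce positive correlation within therapy groups, the naive standard error is too small. For groups of 5 and an assumed ICC of 0.02 to 0.10, this means a true one-sided type I error of about 5.3% to 6.7%, a true SE about 2% to 11% above the naive one at the planning rates, and 2 to 8 points of power.

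The size rests on the assumed ICC, on 150 men per arm and on roughly equal groups. A borderline result could change: a naive one-sided p of 0.04 (z = 1.751) becomes about 0.055 at ICC 0.10 (1.751/1.095 = 1.598). The plan should be changed, but this is not a fatal flaw. The sample-size discrepancy is larger and should be handled separately.

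**What to change.** 1. Record the therapy group to which each intervention man is assigned, and keep him in it for analysis whatever his attendance. If this is not recorded, the correction may be impossible later.
2. Test the primary difference in proportions with cluster-robust variance and a small-sample correction. Each therapy group is one cluster, and each comparison man is a cluster of one.
3. Apply the same approach to the secondary analyses.
4. Report the estimated ICC, and keep the plain chi-square as a sensitivity analysis.

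A binomial model with a random group effect in the intervention arm is a weaker choice here. Groups of 5 at 14% to 23% abstinence hold about one event each (0.7 to 1.15), so the variance component would be unstable. The model also yields a conditional odds ratio, not the planned difference in proportions.

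**Cost:** one extra data field, a reworded analysis section, a slightly larger standard error and a small loss of nominal power. Recruitment, delivery and follow-up are unchanged.
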